### Sample Size

Seventy participants will be recruited to the trial. Power analysis was conducted using G Power 2.0 for the mental health primary outcome variables (social anxiety and depression), with estimates based on published means and standard deviations and reported effects of similar interventions [32]. The analysis indicated that a minimum of 27 to 45 participants per group would be required to detect moderate changes with 80% power in social anxiety and depression (standardized Cohen *d* of 0.43 to 0.57). Owing to funding constraints, only 35 participants will be recruited to each arm.

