### Materials

Table 1 presents the SPIRIT schedule of measures in this study. The primary outcomes will focus on the acceptability, feasibility, and safety of the Uprise program, as well as efficacy as indicated by the change in mental health symptoms (depression, anxiety, and stress). The secondary outcomes will include psychological wellbeing, quality of life, loneliness, physical health, emotion regulation, and cognitive and mindfulness processes.

Demographic variables will include age, gender, sexuality, ethnicity, work status, level of education, previously attempted university degrees, current university course load, postcode, and religion. The Lubben Social Network Scale-12 items (LSNS-12 [34]) will be used as a demographic assessment of the participants’ risk of social isolation. The Positive and Negative Affect Schedule-Trait (PANAS [35]) will be used as a measure of trait-level positive and negative affect.

**Table 1 table1:** SPIRIT schedule of enrolment, interventions, and assessments.

Variable		Study period							
		Enrolment	Baseline	Postallocation				Close out	
				Waitlist	End of waitlist	Uprise	End of treatment	3-month follow-up	
Timepoint		T0	T1	N/A^a^	T2	N/A	T3	T4	

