#### Mental Health

Psychological distress will be measured with the Kessler Scale of Distress-10 items (K10 [36]). Depression will be measured with the Centre for Epidemiological Studies-Depression (CES-D [37]) and depression subscale of the Depression Anxiety Stress Scale-21 items (DASS-21 [38]). Anxiety will be measured with the anxiety subscale of the DASS-21, and social anxiety will be measured with the 20-item Social Interaction Anxiety Scale (SIAS [39,40]).

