To assess short-term treatment effects, the trajectory of change in each of the outcomes will be examined from baseline (T1) to the end of waitlist (T2) for the waitlist group and from baseline (T1) to the end of treatment (T3) for the intervention group. The trajectory of change in each of the outcomes will be compared between groups. Each analysis will include time (fixed), group (fixed), and the fixed interaction between time and group (time × group) as predictors. A significant time × group interaction effect will indicate a differential rate of change in outcomes between the groups from baseline (T1) to the end of waitlist (T2)/end of treatment (T3).

To assess long-term treatment effects, the trajectory of change in outcomes from baseline (T1) to 3-month follow-up (T4) will be examined in the intervention group only. Sensitivity analysis will also be conducted to determine the trajectory of change from baseline (T1) to 3-month follow-up (T4) in the waitlist group only.

Secondary analyses will include per protocol analysis (only those who complete the four core modules within 6 weeks) and analyses controlling for moderator variables (eg, age, sex, baseline symptom severity, number of Uprise program modules completed, number of coaching calls completed, and number of days accessing the platform). We will report 95% confidence intervals for each test statistic.

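### The protocol does not fix which scale answers its primary efficacy aim; the five or six scales testable between arms carry roughly a 15–26% chance of at least one false positive

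*Protocol article*

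**What the plan says.** The Introduction puts efficacy in reducing mental health symptoms within the primary aim, beside acceptability, feasibility and safety. The protocol then describes the primary efficacy outcome in three ways.

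- **Sample Size** reports a power analysis "for the mental health primary outcome variables (social anxiety and depression").
- **Materials** gives the primary efficacy outcome as "efficacy as indicated by the change in mental health symptoms (depression, anxiety, and stress"). The Results paragraph of the Abstract gives the same three domains.
- **Primary Outcomes** (subsections Mental Health and Stress) lists eight scales: K10, CES-D, DASS-21 depression, DASS-21 anxiety, SIAS, PSS-4, DASS-21 stress and the modified SDS. Depression has two instruments, CES-D and a DASS-21 subscale. Stress also has two, with the modified SDS under the same subheading. General distress, which is in neither shorter list, is included too: "Psychological distress will be measured with the Kessler Scale of Distress-10 items".

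Planned Data Analysis applies one model per outcome: "The trajectory of change in each of the outcomes will be compared between groups". The contrast runs "from baseline (T1) to the end of waitlist (T2) for the waitlist group and from baseline (T1) to the end of treatment (T3"), the second span being that of the Uprise arm. Each model is read by its interaction term: "A significant time × group interaction effect will indicate a differential rate of change in outcomes between the groups". The section names no lead scale and no order among the scales. The only indication of a test level is "We will report 95% confidence intervals for each test statistic".

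**The concern.** The choice of primary outcome belongs in the protocol, and here three sections give three different lists. A reader of the eventual report could not tell from the protocol which interaction term was meant to answer the efficacy question. If the depression scales disagree, or social anxiety moves and stress does not, nothing in the text says which result counts.

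Two things are at stake. With several overlapping scales each read at the conventional level, one significant interaction can arise by chance and be reported as support for efficacy. The instrument given prominence could also be chosen after the results are known. The timetable sharpens this: data collection ended in December 2019 and the final analysis was expected by November 2020, so any choice still open would be made with outcome data already collected.

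**Working it through.** **Step 1: which scales can be tested between arms.** The comparison needs a baseline value and a value at T2 (waitlist) or T3 (intervention). Table 1 gives:

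| Scale | Scheduled at | Can enter the comparison? |
|---|---|---|
| CES-D | T1, T2, T3, T4 | Yes |
| DASS-21 depression | T1, T2, T3, T4 | Yes |
| DASS-21 anxiety | T1, T2, T3, T4 | Yes |
| DASS-21 stress | T1, T2, T3, T4 | Yes |
| SIAS | T1, T2, T3, T4 | Yes |
| K10 | T0, T2, T3, T4 | Only with its T0 value as baseline |
| PSS-4 | Uprise column only | No T1 or T2 value |
| Modified SDS | Uprise column only | No T1 or T2 value |

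The number of testable scales is therefore m = 5, or m = 6 with K10.

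**Step 2: the test level.** The protocol states no alpha and no family-wise error rate, so there is no stated error figure to reproduce. Two-sided 5% per test is an assumption taken from the 95% confidence intervals. The stated 27 to 45 per group is consistent with it: a paired t test at two-sided 5% and 80% power needs 26.1, rounded up to 27, at d = 0.57 and 44.4, rounded up to 45, at d = 0.43. That this figure matches a within-group rather than a between-group test is a separate matter.

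**Step 3: independent tests, no true effect on any scale.** P(at least one p < 0.05) = 1 − 0.95^m.

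- m = 5: 1 − 0.7738 = 22.6%
- m = 6: 1 − 0.7351 = 26.5%

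**Step 4: correlated tests.** The protocol gives no correlations, so a range is assumed. With a common correlation r between the test statistics and c = 1.96,

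P = 1 − E[{Φ((c − √r·U)/√(1−r)) − Φ((−c − √r·U)/√(1−r))}^m], U standard normal, by numerical quadrature.

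| r | m = 5 | m = 6 |
|---|---|---|
| 0 | 22.6% | 26.5% |
| 0.5 | 18.3% | 20.7% |
| 0.6 | 16.7% | 18.7% |
| 0.7 | 14.8% | 16.4% |
| 0.8 | 12.7% | 13.9% |

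**Step 5: false benefit only.** One tail at 2.5% per test, m = 6: 1 − 0.975^6 = 14.1% if independent, 10.4% at r = 0.5 and 8.2% at r = 0.7.

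**Step 6: the powered outcomes against the declared ones.**

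| Domain | Sample Size | Abstract and Materials | Primary Outcomes |
|---|---|---|---|
| Depression | Yes | Yes | Yes (two scales) |
| Social anxiety | Yes | Not named | Yes (SIAS) |
| General anxiety | No | Yes (as anxiety) | Yes (DASS-21) |
| Stress | No | Yes | Yes (DASS-21, PSS-4; modified SDS alongside) |
| Distress | No | No | Yes (K10) |

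The powered outcomes are a subset of the Primary Outcomes section but do not match the headline list.

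**The case against.** **An analysis plan may settle it.** Error control and test order are commonly left to an SAP, and this is a condensed article. Their absence alone would not be a finding. What stands is that the article contradicts itself on which outcomes are primary, and an SAP would have to choose between its lists. The error rates in the working apply if no such rule was fixed elsewhere.

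**It is a pilot.** Acceptability, feasibility and safety are also primary and are assessed descriptively, and strict family-wise control is not always expected in a pilot. This lowers the weight of the point but does not remove it, because the protocol itself makes efficacy primary, bases its power analysis on it and reads the tests by significance.

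**Stronger readings that a reader might infer, and that the protocol does not support:**

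- *Eight tests, hence about 34%.* That is 1 − 0.95^8 = 33.7%. It needs eight independent tests. PSS-4 and the modified SDS have no T1 or T2 value, and independence is implausible when three scores come from the DASS-21 and depression is measured twice.
- *A rule that any one significant scale establishes efficacy.* None is written. The quoted sentence interprets a model term; the risk comes from having no rule that fixes the answer.
- *The trial was powered on outcomes that are not primary.* Depression and social anxiety both appear under Primary Outcomes. The mismatch is with the headline list, and it does not cause the raised error rate.

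**The two-sided rate includes errors in the direction of harm.** This is correct. The false-benefit figures in the working are the fairer measure of a mistaken efficacy claim, and they still exceed the nominal 2.5%.

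**Conclusion.** The concern holds in a limited form. The protocol does not fix which scale answers its primary efficacy aim, and its sections disagree on the primary set. Taken as written, with five or six scales testable between arms, the chance of at least one false-positive primary scale is about 15–26%, roughly three to five times nominal. For false benefit alone on six scales it is about 8–14% against 2.5%.

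These figures rest on a two-sided 5% level that is inferred, on no true effect on any scale, and on an assumed common correlation between 0 and 0.7. A correlation of 0.8 would bring the two-sided rate down to 12.7% or 13.9%. The mismatch between the power analysis and the headline list is a second, separate inconsistency: social anxiety is missing from the headline list, and general anxiety and stress are not in the power analysis.

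**What to change.** Before the outcome data are analysed, and with a statement that results were unseen when the choice was made:

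1. Name one lead efficacy scale that is measured in both arms at T1 and at T2/T3 and lies in a powered domain, tested at two-sided 5%. CES-D is one example. Sample Size names the domain and not the instrument, so the choice between CES-D and DASS-21 depression is the sponsor's to make and record.
2. Put SIAS second in a fixed sequence, or apply Holm across the two scales (smaller p-value against 0.025, then the other against 0.05). Either keeps the family-wise rate at or below 5%. Testing both unadjusted would give up to 1 − 0.95² = 9.75%.
3. Report the remaining symptom, stress and impairment scales as supportive, with estimates and 95% confidence intervals and no significance claim.
4. Align the Abstract, Sample Size, Materials and Primary Outcomes to that list.

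No new data are needed. The other scales lose confirmatory status, a modest loss in a pilot. The change comes after data collection ended, so it has to be recorded openly as an amendment. Research Governance and Ethics sends major amendments to the ethics committee and the trial registry.

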## Methods

### Trial Design

The study will be a pilot randomized waitlist-controlled trial, with two parallel groups, using a 1:1 allocation ratio. Waitlist was selected as the control condition to enable comparison of the Uprise program to students’ usual daily life, while ensuring that all participants had the opportunity to access the Uprise program. Figure 1 presents the study design.

Participants will initially undergo screening for eligibility via telephone interview (T0). Eligible participants will be invited to complete the baseline assessment (T1). Informed consent will be obtained at the baseline assessment. Following the baseline assessment, each consenting participant will be randomized to either the Uprise program or waitlist for the following 4 weeks. Those allocated to the Uprise program will be given access to the program and asked to complete one module per week across the following 4-week period. At the end of the program, these participants will be invited to complete an end-of-treatment assessment (T3). Participants allocated to waitlist will be asked to continue with their usual activities across the following 4-week period, at the end of which they will be invited to complete an end-of-waitlist assessment (T2). Waitlist participants will then be given access to the Uprise program and asked to complete one module per week for the following 4 weeks, at the end of which they will be invited to complete an end-of-treatment assessment (T3). Participants will also be invited to complete a semistructured interview at the end-of-treatment (T3) assessment regarding their experience with the intervention. The interview will be recorded and later transcribed for qualitative analysis. All participants will be invited to complete a follow-up assessment (T4) 3 months after their end-of-treatment (T3) assessment.

The Consolidated Standards of Reporting Trials (CONSORT) flow diagram of the study procedure is shown in Figure 1. The protocol was designed in accordance with the Standard Protocol Items: Recommendations for Interventional Trials (SPIRIT) and good clinical practice (GCP) guidelines (see Multimedia Appendix 1 and Multimedia Appendix 2 for relevant checklists).

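### The long-term treatment effect is an uncontrolled pre-post change in one arm, and its waitlist sensitivity analysis starts at T1, before four untreated weeks, instead of at programme start

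*Protocol article*

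**What the plan says.** The Planned Data Analysis section of the protocol article separates two questions. The short-term analysis compares the arms through a time × group interaction, from T1 to T2 on waitlist and from T1 to T3 on Uprise. The long-term analysis has no such term. It opens with "To assess long-term treatment effects" and continues: "the trajectory of change in outcomes from baseline (T1) to 3-month follow-up (T4) will be examined in the intervention group only". The supporting check is: "Sensitivity analysis will also be conducted to determine the trajectory of change from baseline (T1) to 3-month follow-up (T4) in the waitlist group only".

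The Trial Design section fixes what each arm receives in these windows. For T1 to T2: "Participants allocated to waitlist will be asked to continue with their usual activities across the following 4-week period". After T2: "Waitlist participants will then be given access to the Uprise program and asked to complete one module per week for the following 4 weeks". Everyone is then invited to a "follow-up assessment (T4) 3 months after their end-of-treatment (T3) assessment". On numbers, the Sample Size section says "only 35 participants will be recruited to each arm".

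**The concern.** There are two linked problems.

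**The label.** Once the waitlist arm has crossed over, both arms have had the programme, and randomisation no longer supplies a contrast at T3 or T4. A T1 to T4 change in one arm mixes any programme effect with natural fluctuation, repeated testing and time of year. The article itself gives reasons to expect movement without treatment. Entry is restricted by a distress score and by recent symptoms, and people excluded for symptom severity may be screened again later (Eligibility Criteria). Recruitment ran from October 2018 to June 2019 and data collection ended in December 2019 (Results), so follow-up falls at different points of the academic year. Because high scorers are excluded, regression to the mean could even work against the programme. The direction of the bias is therefore unknown.

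**The check.** A sensitivity analysis should estimate the same quantity under different assumptions. This one changes the arm and also the exposure in the window. If the two results differ, the waiting period alone could be the reason. If they agree, offsetting drift could be the reason.

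Efficacy is among the trial's primary aims, so a follow-up result presented as a treatment effect could be read as evidence of lasting benefit that the design cannot give.

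**Working it through.** The plan gives no figure for the T4 analysis, so there is none to reproduce. The checks below are the window lengths, the consequence of having no control, the effect of the T1 origin, and the possible gain from pooling.

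**1. Window lengths.** Inputs: waitlist period 4 weeks (Trial Design); programme 4 weeks (Trial Design) or 4 to 6 weeks (Planned Intervention); T4 is 3 months after T3, where 3 months = 3 × 365.25 / 12 / 7 ≈ 13.0 weeks. The up to 7 days allowed for allocation are ignored.

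| Window | Formula | 4-week programme | 6-week programme |
|---|---|---|---|
| Intervention, T1 to T4 | programme + 13.0 | 17.0 | 19.0 |
| Waitlist, T1 to T4 | 4 + programme + 13.0 | 21.0 | 23.0 |
| Waitlist, T2 to T4 | programme + 13.0 | 17.0 | 19.0 |
| Untreated share of waitlist T1 to T4 | 4 / window | 4/21.0 = 19% | 4/23.0 = 17% |

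The waitlist window that matches the intervention arm is T2 to T4. Table 1 schedules T2 for nearly every outcome measured at T1, so this origin is available.

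**2. No control at T4.** Suppose the programme does nothing and scores drift by δ, in SD units of the change score. A pre-post t test with n = 35 at two-sided 0.05 (assumed, in line with the planned 95% intervals) has 34 degrees of freedom and noncentrality δ√35; for δ = 0.3 this is 1.77. The article gives no drift figure, so δ is an assumed range.

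| δ | 0 | 0.1 | 0.2 | 0.3 | 0.4 | 0.5 |
|---|---|---|---|---|---|---|
| P(significant) | 0.05 | 0.09 | 0.21 | 0.41 | 0.63 | 0.82 |

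These values assume that all 35 have T4 data.

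**3. Effect of the T1 origin.** Illustration with assumed values: a programme change of −1.0 between programme start and end, held to T4, and a waiting-period drift of 0, −0.2 or −0.3. Programme length is 4 weeks.

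- Total change from T2 to T4 is −1.0 in each case. From T1 to T4 it is −1.0, −1.2 and −1.3.
- If one straight line in time is fitted, the slope from T2, T3 and T4 is −0.0441 per week, the same as the intervention arm's slope from T1, T3 and T4. The slope from T1, T2, T3 and T4 is −0.0501, −0.0567 and −0.0600. These are steeper by 0.0501/0.0441 − 1 = 14%, then 29% and 36%.

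So a linear slope differs between the arms even with identical programme effects and no drift.

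**4. Pooling on programme start.** The ratio of interval widths is √(35/70) = 0.71, about 29% narrower. This assumes equal T4 retention and equal change variance. With an assumed retention of 70% in the intervention arm and 50% on waitlist, the numbers are 24.5 and 17.5. Then √(24.5/42) = 0.76, about 24% narrower.

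**The case against.** The strongest defence is that the missing control is inherent and disclosed. Waitlist was chosen so that everyone could have the programme, the text says plainly that only one arm is used, and no between-arm claim is planned at T4. That is right, and it confines the first part of the point to the label and the conclusion drawn. No analysis of these data can supply a T4 control.

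A reader might also infer that the plan definitely counts the four waiting weeks as treatment time. The article does not support this. It does not say how time is coded in this model or whether T2 enters as its own point. With categorical or piecewise time, T1 to T2 would be estimated separately. No such term is stated and T1 is named as the origin, so the misalignment is conditional on the coding.

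Nor is it right that the two results would be beyond interpretation. The waitlist T1 to T2 change is already estimated in the short-term model and summarised descriptively, so a reader could set it against the T1 to T4 result.

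Finally, T2 is not a neutral baseline. It follows randomisation, in participants who know that they are waiting, and some may have left by then. T1 is the common pre-randomisation assessment. This makes pooling partly a modelling preference, but it does not make T1 the better origin for change over the programme.

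**Conclusion.** The point holds in two parts. First, a single-arm change in at most 35 people is called a treatment effect when no untreated comparator exists after T2. This follows directly from the text. Second, the waitlist check covers about 21 weeks against 17 (23 against 19), with 17 to 19% of it untreated. It does not target the same quantity unless T1 to T2 is a separate segment. The week counts rest on 3 months being 13 weeks. The false-positive probabilities rest on an assumed drift and show what could happen, not what did.

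It would go too far to read this as a flaw in the trial's efficacy comparison: the randomised time × group analysis is untouched. A 29% gain in precision from pooling is a ceiling, not an expectation. Nor can every outcome be realigned. As Table 1 schedules them, PSS-4, modified SDS and WHO-5 appear only in the Uprise column and at none of T1 to T4, and K10 has T0 in place of T1.

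**What to change.** - Describe the T4 result as uncontrolled within-participant change after the programme, and draw no causal conclusion about long-term efficacy from it.
- Start the waitlist follow-up trajectory at T2 (T2, T3, T4) to match the intervention arm (T1, T3, T4). Report the waitlist T1 to T2 change beside it as the untreated drift. State how time is coded.
- Optionally, add a pooled model aligned on programme start, with arm and arm × time terms, as a supportive analysis, and show each arm separately. It adds precision but not a control.
- Limit this to outcomes scheduled at these visits. For K10, use T0 as the intervention arm's baseline. State that PSS-4, modified SDS and WHO-5 cannot be analysed this way under Table 1.

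**Cost.** Wording and model specification only; no new assessments for the outcomes covered. Data collection is reported as complete, so the change should be recorded as made after it ended. The follow-up claim becomes more modest, and T2 as a post-randomisation baseline may carry waiting effects and early dropout, which should be acknowledged.

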### Planned Data Analysis

Summary data will be provided to describe the number of participants who registered interest in the trial, the number deemed ineligible for the trial and why, and the number who completed each stage of the trial.

Data will be analyzed on an intention-to-treat basis (ie, including all enrolled participants regardless of whether they completed the trial). Acceptability, feasibility, and safety will be evaluated using descriptive statistics. Qualitative interviews will be analyzed using the six-step approach by Braun and Clarke [55] for qualitative data analysis to identify and develop themes from the data to further inform about the acceptability of the intervention to participants.

Results will be summarized as means and standard deviations (or median and range/percentage and number as appropriate) for both groups at baseline (T0) and for the relevant group at the end of waitlist (T2)/end of treatment (T3) for all outcome measures. For both groups, this will demonstrate their results at baseline and again 4 weeks after baseline.

Additionally, the *t* test and chi-square test will be used to evaluate baseline group differences in all demographic and outcome measures. This will be performed to compare the waitlist and intervention groups, and to compare those who drop out from the trial to those who complete the trial. This will enable identification of potential baseline moderator variables or factors that contribute to attrition that can be included as covariates in subsequent analyses.

Multilevel linear mixed effects modeling (MLM) will be used to assess acute and long-term treatment effects in each of the outcome measures. MLM is a regression-based approach that is robust to missing data and provides a more powerful means of analyzing longitudinal data than the ANOVA family of analyses [56]. MLM is robust to missing data because it does not delete cases list-wise due to missing data, but instead includes all available data points for each participant. Missing data analysis will be conducted to determine whether data are missing completely at random. If it is identified that data are missing not at random, covariates will be added to all models to account for systematic variation related to missingness.

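### Usage counts and the completer set are not confined to within-arm analyses, although in the short-term group comparison they are consequences of allocation and zero by design on waitlist

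*Protocol article*

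**What the plan says.** All references are to the protocol article.

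- **Main analysis (Planned Data Analysis).** "Data will be analyzed on an intention-to-treat basis". The short-term effect is the interaction in a mixed model with time, group and their product: "A significant time × group interaction effect will indicate a differential rate of change in outcomes between the groups". It runs from T1 to T2 on waitlist and from T1 to T3 in the intervention arm.
- **Long-term analysis (same section).** The T1 to T4 trajectory "will be examined in the intervention group only", with a sensitivity analysis in the waitlist arm alone.
- **Secondary analyses (same section).** One is a "per protocol analysis (only those who complete the four core modules within 6 weeks"). The other is "analyses controlling for moderator variables", with examples that run from age, sex and baseline severity to "number of Uprise program modules completed, number of coaching calls completed, and number of days accessing the platform". The text does not say which of the models above either one applies to.
- **Exposure (Trial Design).** "Participants allocated to waitlist will be asked to continue with their usual activities across the following 4-week period". After T2, "Waitlist participants will then be given access to the Uprise program and asked to complete one module per week for the following 4 weeks".

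**The concern.** The list of covariates mixes two kinds of variable. Age, sex and baseline severity are fixed before allocation. Modules, coaching calls and platform days arise after allocation and, up to T2, only in the arm given Uprise. Conditioning a randomised contrast on such variables conditions on part of the treatment itself.

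The completer rule has a related difficulty. It can be met by T3 in the Uprise arm, but nobody on waitlist can meet it by T2. The waitlist side of a short-term per-protocol comparison must therefore be everyone, no one, or those who completed later, after the T2 outcome was recorded.

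At stake is how the secondary efficacy results are read. An adjusted analysis could appear to show that a real effect has vanished or reversed, and a completer analysis could flatter the program.

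**Working it through.** The plan states no figure on this point, so there is none to reproduce. The only design number used is 35 per arm (Sample Size). Usage levels, completion rates and their link to prognosis are assumptions. Effects are in SD units and positive means benefit.

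**1. Where a group effect exists.** Of the three planned models, only the short-term one has a group term. In the two T1 to T4 models usage is well defined, because the waitlist arm receives Uprise after T2, and there is no group effect to distort.

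**2. Usage as a main effect.** Let G be group, M modules completed and t = 0, 1:

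Y = b0 + b1·t + b2·G + b3·t·G + c·M + person effect + error.

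The within-person change is b1 + b3·G + error. M does not vary over time, so it cancels, and with complete data b3 is the plain difference in mean change. A random-intercept simulation (150 runs, 35 per arm, true effect 0.5) gave 0.514 (SE 0.249) both with and without M. With 20% missing follow-up it gave 0.498 without M and 0.499 with M.

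**3. Usage with time, or in a change-score model.** The change becomes b1 + b3·G + d·M + error. Since M = 0 whenever G = 0, b3 compares an Uprise participant who used nothing with the waitlist. The intention-to-treat (ITT) difference is b3 + d × mean(M). If a true 0.5 acts wholly through modules and mean use is 2.7 of 4, then d = 0.5/2.7 = 0.185 and b3 = 0.5 − 2.7 × 0.185 = 0.

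Collinearity, assuming a mean of 3 and SD of 1.2 modules in the Uprise arm and 0 on waitlist:
- variance between arms: 0.25 × 3² = 2.25
- variance within arms: 0.5 × 1.2² = 0.72
- R² = 2.25/2.97 = 0.758
- variance inflation = 1/(1 − 0.758) = 4.1, so the SE is multiplied by about 2.0

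**4. Simulation.** There were 4,000 replicates with 35 per arm and a linear model on change. A latent trait drives module use and also drives improvement with strength g.

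| Truth | g | ITT | Adjusted for modules | Uprise completers vs all waitlist | Completers in both arms |
|---|---|---|---|---|---|
| No effect | 0 | 0.01 | 0.02 | 0.00 | 0.01 |
| No effect | 0.3 | 0.00 | −0.44 | 0.22 | 0.02 |
| No effect | 0.5 | 0.00 | −0.72 | 0.35 | 0.00 |
| 0.5 through modules | 0 | 0.51 | 0.00 | 0.74 | 0.74 |
| 0.5 through modules | 0.3 | 0.50 | −0.44 | 0.95 | 0.74 |
| 0.5 through modules | 0.5 | 0.51 | −0.73 | 1.11 | 0.75 |
| 0.5 regardless of use | 0 | 0.51 | 0.51 | 0.51 | 0.51 |
| 0.5 regardless of use | 0.3 | 0.50 | 0.08 | 0.71 | 0.49 |
| 0.5 regardless of use | 0.5 | 0.50 | −0.23 | 0.85 | 0.51 |

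The SE was about 0.24 for ITT and 0.48 to 0.50 after module adjustment. The last column uses the waitlist arm's later completion and assumes that neither waiting nor the T2 result affects it.

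**5. Completer selection by formula.** If a share p completes and completion propensity correlates r with untreated improvement, completers differ from all participants by r·φ(z_p)/p.
- p = 0.5: 0.399/0.5 = 0.798, so r = 0.2 to 0.3 gives 0.16 to 0.24.
- p = 0.7: 0.348/0.7 = 0.497, so r = 0.2 to 0.3 gives 0.10 to 0.15.

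**The case against.** The strongest reply is that the plan does not commit to a damaging model. Its treatment effect is the time × group term, and a usage total added as an ordinary covariate leaves that term alone (step 2). The loss of effect and the doubled SE need a usage × time term or a change-score model, and the article specifies neither. The usage variables are offered as examples and called moderators, which suits a dose-response question in the within-arm models, where they are well defined. A completer set with a prespecified threshold is a conventional secondary analysis, and the exact waitlist set could be left to a fuller plan. The main analysis is by intention to treat.

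Most of this stands, and it rules out two stronger readings that a reader might infer. One is that both secondary analyses necessarily bias the group effect. They do not: a main effect is inert, and the completer comparison is unbiased under the null when completion is unrelated to prognosis. The other is that usage is undefined for the waitlist throughout the trial. That is true only up to T2.

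What does not stand is the inference that no change is needed. The article itself names the usage counts beside baseline variables in an adjustment analysis and does not confine them to within-arm models. For the group contrast the result is either inert or misleading, so nothing is lost by excluding them.

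**Conclusion.** The point holds for the secondary analyses only. Adjusting the short-term group comparison for modules, calls or platform days cannot improve it. As a main effect usage does essentially nothing. With time, it changes the question to the effect at zero use, which took a true 0.5 SD to between 0.00 and −0.73 when the effect acted through modules, and roughly doubled the SE. The completer rule cannot be applied to the waitlist by T2, and setting Uprise completers against all waitlist participants favours Uprise if completion is related to prognosis: by 0.10 to 0.24 SD from the formula, or 0.22 to 0.35 SD in the simulation under no effect.

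These sizes are illustrative. They rest on assumed usage, completion and selection, none of which the documents give. A reader might conclude that the trial's main efficacy result is compromised. The documents do not support that, because the intention-to-treat time × group analysis uses neither the usage counts nor the completer set.

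**What to change.** In Planned Data Analysis:

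1. Adjust the between-group model only for covariates fixed before randomisation: age, sex and baseline severity.
2. Use modules, coaching calls and platform days only in exploratory dose-response analyses within an arm, described as associations.
3. Do not present completers versus all waitlist as a treatment effect. Label it non-randomised and exploratory, and state which waitlist participants it uses.
4. Optionally supplement it with a complier-average estimate that uses allocation as the instrument and keeps all waitlist participants.

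Items 1 to 3 cost only wording. The Results section reports data collection finished with the final analysis still to come, so no new data are needed. Item 4 is one extra model and a real trade-off. The estimate is roughly the ITT effect divided by the completion share, so at an assumed 50% to 70% completion its SE grows by about 1/0.7 = 1.4 to 1/0.5 = 2.0 times (0.24 becomes about 0.34 to 0.48). It also needs the exclusion restriction, that partial use or coaching without completion has no effect. That is doubtful where coaching is optional and partial use is possible, so the assumption must be stated with the result.
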